#### Secondary Efficacy Endpoints

##### Outcomes Collected From the RTI Symptom Diaries

Participants will use a validated self-reported RTI symptom diary, used in previous studies by the research team [40]. Each symptom will be graded on a 7-point Likert scale (0=not affected; 1=very little problem; 2=slight problem; 3=moderately bad; 4=bad; 5=very bad; 6=as bad as it could be). Symptoms recorded include cough, phlegm, shortness of breath, wheeze, blocked/runny nose, facial pain, chest pain, sensation of fever (high temperature), muscle aching, headache, disturbed sleep, feeling generally unwell, and interference with normal activities/work. Participants will rate symptoms for 14 days and return the diary upon completion (electronically or paper-based). It will document daily antibiotic doses and other therapies. For patients who do not return diaries, a short form asking about how many days antibiotics were actually taken, whether antibiotics have been taken after being discontinued by their doctors, and details of the duration and severity of symptoms will be completed by a telephone call to the patient at day 14.

Duration of antibiotic therapy, in days, defined as the number of days until discontinuing treatment in both groups (mean/median)Use of antibiotics other than the study medication and other symptomatic therapies within the first 2 weeks (mean/median)Early clinical assessment based on the overall score at Day 7, defined as the total symptom score reported by the patient on that day (mean/median)Duration of severe symptoms, in days, defined as the number of days until the last day the patient scores 5 in any of the symptoms (mean/median)Duration of moderate symptoms, in days, defined as the number of days until the last day the patient scores 3 in any of the symptoms (mean/median)Total resolution of symptoms, in days, defined as the number of days until the last day the patient scores 0 in all the symptoms (mean/median)The duration of antibiotic therapy, in days, defined as the number of patients discontinuing treatment in both groups, and day they discontinue will also be checked via electronic medical records

Outcomes 1 to 7 from the RTI symptom diary will be calculated for each participant every day from day 0 until day 14 or when the participant has scored 0 for every item, whichever comes first.

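### Severe and moderate symptom durations are tied to scores of exactly 5 and exactly 3, and the rule that rescues the total-resolution wording discards symptoms that return

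*Protocol article*

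**What the plan says.** All the relevant text is in the protocol article, Outcomes Collected From the RTI Symptom Diaries.

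- **Scale.** Each symptom is graded 0 to 6, with the upper grades labelled "3=moderately bad; 4=bad; 5=very bad; 6=as bad as it could be".
- **Severe duration.** "the number of days until the last day the patient scores 5 in any of the symptoms".
- **Moderate duration.** "the number of days until the last day the patient scores 3 in any of the symptoms".
- **Total resolution.** "the number of days until the last day the patient scores 0 in all the symptoms".
- **Calculation window.** The closing sentence has the diary outcomes calculated "every day from day 0 until day 14 or when the participant has scored 0 for every item, whichever comes first".
- **Recording period.** "Participants will rate symptoms for 14 days and return the diary upon completion".

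No other section gives a threshold or a range of scores for severe or moderate. The Objectives section lists the three durations as secondary objectives.

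**The concern.** An outcome called duration of severe symptoms should not end earlier because a symptom is at the worst grade instead of the one below it. A rule that looks for a 5 does exactly that: a 6 does not meet it. Likewise a 4, labelled one step worse than moderately bad, does not meet the rule for moderate.

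For total resolution, the last all-zero day is not when symptoms ended. It is the last day on which the patient was still well. The closing sentence repairs this by stopping at the first all-zero day, but the same stop removes whatever the patient records afterwards. The Discussion (Principal Findings) names avoiding relapse as the central difficulty in deciding when antibiotics can stop. If stopping early did lead to more returning symptoms, these outcomes would be slow to show it.

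The Blinding section also says that keeping outcome assessors and data analysts blind to allocation is difficult. An analyst who silently reads 5 as 5 or more would be changing a published definition, possibly knowing the allocation. The definition is better settled beforehand.

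**Working it through.** The article states no figure for these outcomes, so there is none to reproduce. The check applies the written rules to example diaries.

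**Inputs.** The 0 to 6 scale, the three rules and the calculation window come from the section above. The diaries are assumptions: each lists the worst item score from day 0, with 0 from the last entry shown to day 14. They also assume that no other item stands at exactly 5 or exactly 3 on a day that would change the result.

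**Formulas.**
- Severe as written: latest day with some item = 5. With a threshold: latest day with some item ≥ 5.
- Moderate as written: latest day with some item = 3. With a threshold: latest day with some item ≥ 3.

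| Diary | Worst score by day | Severe, = 5 | Severe, ≥ 5 | Moderate, = 3 | Moderate, ≥ 3 |
|---|---|---|---|---|---|
| A | 6,6,5,5,4,4,3,3,2,2,1,0 | day 3 | day 3 | day 7 | day 7 |
| B | 6,6,6,6,4,4,4,2,2,1,0 | none | day 3 | none | day 6 |
| C | 4,4,4,4,4,2,2,1,0 | none | none | none | day 4 |
| D | 5,6,6,6,6,2,2,1,1,0 | day 0 | day 4 | none | day 4 |
| E | 3,4,4,4,4,4,2,1,0 | none | none | day 0 | day 5 |

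Diary A passes through every grade and the two versions agree. Diaries B to E skip 5 or 3 on the way down. Their durations as written are undefined, or too short by 4 days (D, severe: 4 − 0) and 5 days (E, moderate: 5 − 0).

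**When the versions differ.** They agree if, on the last day with any item at 5 or more, some item is exactly 5; the same holds for 3. In B, a second item at exactly 5 on day 3 and at exactly 3 on day 6 would remove both errors. The diary has 13 items, so this will often help, but nothing guarantees it.

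**Total resolution.** Three versions are compared: the last all-zero day over the whole diary; the same wording with the stop at the first all-zero day; and the first day from which all items stay 0 through day 14. Diary R adds a relapse.

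| Diary | Worst score by day | Wording alone | With the stop | Sustained zero |
|---|---|---|---|---|
| A | 6,6,5,5,4,4,3,3,2,2,1,0 | day 14 | day 11 | day 11 |
| R | 5,4,3,1,0,3,3,2,0 | day 14 | day 4 | day 8 |

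Without a relapse the stop gives the sensible answer. In R it places resolution 4 days early (8 − 4). It also cuts moderate duration from day 6 to day 2, because the scores of 3 on days 5 and 6 fall after the stop. Those scores exist, since patients are asked to rate symptoms for the full 14 days.

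**The case against.** **The intent is obvious, and any analyst would use thresholds.** That may be so, but the text does not say it. Moderate could also be meant as 3 to 4 only. A definition that needs silent correction should be corrected openly.

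**The effect may be small.** This stands. A patient gets no severe or moderate day only if none of the 13 items is ever exactly 5 or 3 in the period counted. The examples show that the error is possible, not how often it occurs.

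**Stronger readings a reader might infer.** Three go further than the article supports.
- *Grades 4 and 6 are ignored altogether.* They are not. The day 7 outcome is "defined as the total symptom score reported by the patient on that day", which uses every grade; any 4 or 6 prevents resolution; and days at 6 or 4 before a later 5 or 3 fall inside the elapsed duration.
- *Fast recoverers get the longest resolution time.* The wording alone would give day 14 to a patient symptom-free from day 5, but the closing sentence stops the calculation at day 5. The word 'last' conflicts with that sentence; it does not establish mistiming. The loss of relapses remains.
- *The mean or median will be taken among resolvers only.* The article does not say this. How patients unresolved at day 14 are handled, including any censoring, is commonly left to an analysis plan, which is not at hand.

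**Conclusion.** The point holds in limited form. As written, severe and moderate durations depend on exact scores of 5 and 3. They come out too short or undefined when, on the last day at or above that grade, no item stands exactly on it. Total resolution is worded inconsistently with the sentence that makes it workable, and that sentence discards symptoms returning after a first all-zero day.

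The sizes shown (4 days for severe, 5 for moderate, 4 for resolution after a relapse) come from assumed diaries and are not estimates for the trial. The article gives no data on how often items skip a grade or symptoms return, so neither the average error nor its direction between arms can be calculated.

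The consequence is confined to secondary diary outcomes. The primary endpoint is a day 14 clinical assessment by telephone that does not use these rules, and the sample size rests on that endpoint. Correction before analysis is worthwhile, but this is not a flaw that threatens the main conclusion.

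**What to change.** In Outcomes Collected From the RTI Symptom Diaries:

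1. Define severe duration by the last day with any item at 5 or more.
2. Define moderate duration by the last day with any item at 3 or more.
3. Define total resolution as the first day from which all items remain 0 through day 14.
4. Change the closing sentence so that symptom durations are calculated over the whole diary and do not stop at the first all-zero day. Relapse is then counted.

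The cost is a few lines of wording, best settled before the data are analysed. The diary already collects every item daily for 14 days, so no new data are needed. The primary endpoint and the sample size are unchanged.

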
#### Sample Size

We assumed 85% clinical recovery in the group assigned to the full antibiotic course based on some studies [12,42-44]. Considering a power of 80%, a level of significance of 5%, one-sided noninferiority margin of 10%, as recommended by the guideline on the evaluation of medicinal products indicated for treatment of bacterial infections issued by the European Medicines Agency in 2022 [45], which gave a sample size of 402 patients. Assuming that the primary outcome could not be evaluated in 15% of patients, 474 patients needed to be included in the study (237 in the control group and 237 in the intervention group).

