The concept of “feeling better” is inherently subjective and can vary significantly across individuals, types of infections, and symptom profiles [50]. For some patients, it may indicate partial symptom improvement, while for others it may imply complete resolution of all symptoms. Certain symptoms, such as fever, might be a more reliable indicator for clinical improvement and the safe discontinuation of antibiotics, whereas symptoms like cough may persist longer without significantly impairing daily functioning. Additionally, some patients with RTIs may prefer to stop antibiotics only after full symptom resolution, while others may find the notion of symptom improvement too ambiguous, leading to uncertainty about when to discontinue treatment. To address this challenge, our study defines the appropriate time to stop antibiotic treatment based on a combination of clinical and patient-reported criteria: overall symptom improvement as reported by the patient, normalization of key vital signs—particularly body temperature, and the absence of elevated inflammatory markers, specifically CRP. As a pragmatic randomized clinical trial, this study is designed to provide real-world evidence on how patients interpret and respond to the concept of “feeling better” in the context of antibiotic use. Furthermore, to enhance our understanding, we will conduct a qualitative study with a subset of patients in the intervention group to explore their perceptions and experiences related to symptom improvement and treatment decisions. Insights from this qualitative component will help refine a more practical and clinically applicable definition of when it is appropriate to discontinue antibiotic therapy, ultimately supporting clinicians in providing more precise and consistent advice.

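### Total symptom resolution is summarised by a plain mean/median, but no value is assigned to patients not symptom-free when the 14-day diary ends; leaving them out would bias a delay toward no difference

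*Protocol article*

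**What the plan says.** The protocol article (Outcomes Collected From the RTI Symptom Diaries) lists three durations with the same summary.

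- Total resolution is "defined as the number of days until the last day the patient scores 0 in all the symptoms (mean/median").
- Severe duration is "defined as the number of days until the last day the patient scores 5 in any of the symptoms (mean/median").
- Moderate duration is "defined as the number of days until the last day the patient scores 3 in any of the symptoms (mean/median").

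The diary has 13 items scored 0 to 6, and "Participants will rate symptoms for 14 days and return the diary upon completion". A general rule says the outcomes are calculated daily "until day 14 or when the participant has scored 0 for every item, whichever comes first". Patients who do not return the diary are covered by a short form, in which "details of the duration and severity of symptoms will be completed by a telephone call to the patient at day 14". That fallback has the same 14-day horizon. The section on nonadherence and missing data says only that missing values and outliers will be examined.

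**The concern.** An all-zero day requires every item to clear, including cough, phlegm and shortness of breath. The Limitations section accepts that some symptoms linger: "whereas symptoms like cough may persist longer without significantly impairing daily functioning". Patients with COPD exacerbations are eligible. Some patients in both arms will therefore probably not be symptom-free by day 14, and for them the total-resolution definition yields no day.

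A mean or median taken as written then uses only patients who resolved in time, a group formed after randomization. If stopping antibiotics early slows recovery, some patients move past day 14 and leave the calculation instead of lengthening it. In a noninferiority trial of earlier stopping, bias toward no difference favours the intervention.

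Severe and moderate durations have a different and smaller gap. A patient still scoring at that level on day 14 does have a last day, truncated at 14. A patient who never scores at that level has none, and the protocol does not say whether this counts as 0 or as missing.

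**Working it through.** **The plan's own figure.** The protocol gives none for this outcome: no recovery-time distribution, no share symptom-free at day 14 and no target difference. Its only related figure is in Sample Size: "We assumed 85% clinical recovery in the group assigned to the full antibiotic course". That refers to the primary outcome, which accepts improvement, so it does not give the all-zero share.

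**Illustration (all recovery-time inputs assumed).** Time to the first all-zero day T is lognormal with log-SD s = 0.6, and a share p is unresolved at day 14. Let z = Φ⁻¹(1 − p) and μ = ln 14 − s·z. Then:

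- untruncated mean: M = exp(μ + s²/2)
- mean among resolvers: M·Φ(z − s)/(1 − p)
- restricted mean to day 14: M·Φ(z − s) + 14p

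Control, p = 0.15: z = 1.036, μ = 2.017, M = 9.00, M·Φ(z − s) = 6.02. Resolvers 6.02/0.85 = 7.08; restricted mean 6.02 + 2.10 = 8.12.

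Intervention, p = 0.25: z = 0.674, μ = 2.234, M = 11.18, M·Φ(z − s) = 5.92. Resolvers 5.92/0.75 = 7.90; restricted mean 5.92 + 3.50 = 9.42.

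Differences in days, intervention minus control:

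| Unresolved at day 14 | Untruncated | Restricted to 14 | Resolvers only | Resolvers ÷ restricted |
|---|---|---|---|---|
| 5% vs 10% | 1.52 | 1.22 | 0.89 | 73% |
| 15% vs 25% | 2.18 | 1.31 | 0.82 | 63% |
| 30% vs 40% | 2.16 | 0.90 | 0.53 | 59% |
| 40% vs 50% | 2.36 | 0.75 | 0.45 | 60% |

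The median is affected too. At 15% vs 25% the true medians are 7.52 and 9.34 (difference 1.82). Among resolvers they are 6.71 and 7.72 (difference 1.00).

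**Splitting the loss.** The drop from the untruncated to the restricted difference comes from the 14-day diary, and no analysis recovers it without further assumptions. Only the drop from restricted to resolvers-only comes from leaving patients out. In the 15% vs 25% row that is 1.31 to 0.82 days.

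**Sensitivity.** Simulations varied the shape (exponential; Weibull shape 1.5, 2 and 3; lognormal log-SD 0.3, 0.5 and 0.7), control medians of 6 to 12 days, and delays of 1 or 2 days in the median or a uniform 1-day shift. Dropping unresolved patients retained between 4% and 98% of the untruncated mean delay. Two cases with log-SD 0.5:

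- medians 6 vs 7 days (4.5% vs 8.3% unresolved): 0.73 of 1.13 days retained
- medians 8 vs 9 days (13% vs 19% unresolved): 0.52 of 1.13 days retained

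The mean difference shrank throughout, by an amount that depends on the assumptions.

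**The other reading.** If unresolved patients are recorded as 14 days, the median difference is fully preserved whenever at least half of each arm resolves by day 14. The mean then equals the restricted mean, provided diaries are complete.

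**The case against.** The strongest reply is that nothing in the protocol says unresolved patients are excluded. Calculation runs to day 14, which can be read as recording 14 days. On that reading the median usually survives and the mean is a restricted mean under another name. This stands in part: exclusion is one reading, not stated policy. But the stop rule says when calculation ends, not what is recorded. The two readings give different answers, in a trial whose Blinding section says data analysts are difficult to blind.

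A reader might infer that a true delay would shrink by more than half. The documents do not support that as a general figure. It depends on assumed recovery times, and much of the loss against an untruncated mean comes from the diary length. A reader might also take the 85% recovery assumption to mean that 15% of controls are unresolved here, but it measures a looser outcome.

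Nor does the loss of slow recoverers apply to severe or moderate duration. Patients who never score 5 are milder, and only a 0-or-missing rule is absent. That COPD patients can never reach all zeros is likewise unsupported by any figure, and redefining resolution for them is a separate design choice.

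Finally, censoring methods are often left to an analysis plan, which is not shown here. That is fair for the method. The outcome definition and its summary are fixed in the protocol, however, and the definition is incomplete.

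**Conclusion.** The point holds as a gap in a secondary outcome definition. Total resolution has no value for patients who are not symptom-free by day 14, and the stated summary does not handle them. If they are left out, the direction of bias is clear: a real delay looks smaller. The size is not. Under the lognormal illustration with 15% versus 25% unresolved, a 1.3-day difference observable within 14 days appears as 0.8 days. Those inputs are assumptions, and the loss is small if few patients are unresolved. If unresolved patients are recorded as 14 days, this particular bias does not arise, but the protocol should say so. The primary outcome and the sample size are unaffected. The change is worth making before analysis.

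**What to change.** Define total resolution as the first day on which all items score 0, which is also the day on which the protocol's stop rule ends calculation. Analyse it as time to event in all randomized patients, censored at day 14 or the last diary day. Report Kaplan-Meier medians, the proportion resolved by day 14, and the between-arm difference in restricted mean to day 14.

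For severe and moderate duration, assign 0 days to patients who never score at that level, so that these averages cover all randomized patients with symptom data. Flag as truncated those still at that level on day 14.

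The cost is outcome wording and a little more analysis work, using data already collected. The restricted mean describes only the first 14 days. A Kaplan-Meier median may not be reached if fewer than half of an arm resolve. Censoring at the last diary day also assumes that stopping the diary is unrelated to recovery.

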##### Outcomes Collected From Electronic Case Report Forms, When Available, and From Follow-Up Phone Calls, Which Will Be Cross-Checked With the Patients’ Electronic Clinical Records

Type of antibiotic prescribed and the planned duration.Number of reattendances to any doctor for new or worsening symptoms regarding the infection, within 28 days after the index consultation.Number of complications related to the infection within 28 days after the index consultation, such as visits to emergency departments or hospital admissions regarding the RTI.Number of days of work absenteeism due to the infectious disease, within 28 days after the index consultation.Difference in health-related quality of life on days 14 and 28, compared with baseline, measured using the 5-level EQ-5D version-quality of Life instrument (ie, EQ-5D-5L) [41].Drug-associated adverse events related to the antibiotic, defined as any harmful and unintended health incident—such as a symptom, an abnormal laboratory finding, or worsening of a pre-existing condition—temporally associated with the use of the antibiotic, regardless of whether it is causally related to the treatment, and antibiotics changed within the first 14 days.

##### Other Outcomes

Percentage of patients assigned to the intervention group who feel better and who comply with the criteria for stopping the antibiotic therapy, based on the information collected during the visit to the center

#### Participant Timeline

A flow chart of patients is described in Figure 1. To ensure a standardized and uniform inclusion process, the principal investigator and a senior project manager will inform all participating health care professionals on the inclusion procedures for the study. Eligible participants will be identified as they present to general practice. Once the GP identifies the patient as eligible for the study and a first-line antibiotic with a -lactam is warranted, all the information about the study will be provided, and informed consent will be signed. Details of the ascertainment of visits are provided in Table 3.

**Figure 1 figure1:**
[figure not shown]
Study flowchart of the clinical trial. COPD: chronic obstructive pulmonary disease; CRP: C-reactive protein; RTI: respiratory tract infection; SOFA: sequential organ failure assessment.

**Table 3 table3:** Ascertainment of visits for the clinical trial.

	V1^a^	V2^a^	V3^a^	V4^a^	V5^a^	V6^a^
	Face-to-face visit		Phone call			
	Day 0 (baseline visit)	From day 1^b^ (interv)	Day 3 (±1 day)	Day 7	Day 14	Day 28
Medical history	✓	✓				
Standard physical examination	✓	✓				
Eligibility criteria	✓					
Informed consent	✓					
Prescription of the antibiotic	✓					
Randomization	✓					
EQ-5D-5L questionnaire	✓				✓	✓
Hand-out of the symptom diary	✓					
CRP^c^ rapid testing		✓				
Decision to stop antibiotic course		✓				
Collection of the symptom diary		✓			✓	
Assessment of the clinical efficacy			✓	✓	✓	
Assessment of the drug adherence		✓	✓	✓	✓	
Monitoring of adverse events			✓	✓	✓	✓
Complications, re-attendance			✓	✓	✓	✓

^a^Visits 1-6.

^b^As soon as the patient feels better, only for patients in the intervention group.

^c^CRP: C-reactive protein.

Patient data will be collected at 4 specific time points for patients assigned to the control group and 5 for those allocated to the intervention:

Day 0 (inclusion date at the center): Patients meeting the inclusion criteria will be invited to join the study by their GP. After obtaining informed consent, patients will be randomized into either the control group (receiving a full course of β-lactam therapy for at least 7 days) or the intervention group (instructed to return for assessment upon feeling better and being afebrile). The GPs will complete a case report form on day 0 (inclusion day), recording details such as age, inclusion and exclusion criteria, symptoms, date of symptom onset, comorbidities, concomitant medication, quality-of-life questionnaire (EQ-5D-5L instrument), randomization, assigned group, and details of the antibiotic administered. Patients will also be provided with a symptom diary (web-based or paper-based)From day 1 until the last day of the antibiotic regimen duration (at the center, only for patients assigned to the intervention group): For patients assigned to the intervention, they will be asked to return to the center for clinical reassessment and CRP rapid testing by the professional. Each center will organize ways to make it easy for patients to reach out and schedule an appointment as soon as they feel better (eg, phone number and web-based page). To decide whether to discontinue the antibiotic course when the patient reports feeling better during the consultation, three types of assessment are needed: (1) overall improvement in the patient’s symptoms; (2) signal signs are in normal range (temperature <37 °C; blood pressure >90/60 mm Hg; pulse < 100 beats/minute; respiratory rate <20 breaths/minute, and oxygen saturation >92%), and (3) CRP value is lower than the prespecified values depending on the day of the visit. All this information will be recorded in the electronic case report form (e-CRF; Table 1)Day 3±1 (phone call, only for patients assigned to the intervention group): A reminder phone call for all patients assigned to the intervention group will be made on this day. They will be asked how they feel and reminded to reach out to the center as soon as they feel better for a discontinuation assessmentDay 7 (phone call): An early clinical efficacy outcome will be assessed during this call, including the clinical progression of signs and symptoms, treatment adherence, adverse reactions, any complications, reattendance visits, changes to the assigned treatment or concomitant medication, and the use of antibiotics other than the study drugDay 14 (phone call): The main clinical efficacy outcome and some secondary outcomes, including clinical progression of signs and symptoms, compliance with the study treatment, EQ-5D-5L instrument, adverse reactions, any complications, reattendance visits, changes in the assigned treatment or concomitant medication, including the use of antibiotics other than the study medication, will be assessed. Patients will be asked to return their diariesDay 28 (phone call): Patients will be contacted for information on the number of reconsultations, complications, and the quality-of-life (EQ-5D-5L) instrument

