#### Collection of the Participant Data

We will collect health and personal data from the patients included in the study via REDCap, where the researchers will register basal data and evolution of the illness, and via a patient diary completed by the patients themselves. Regarding the patient’s diary, we will also create a web-based symptoms diary to make it available for all patients recruited. All patients will be able to choose between the web-based and paper version of the symptom diary. Patients will be informed about the type of data that will be collected and about their rights when being informed about the study, and will sign a consent form consenting to the use of their data. No data will be collected before the patient signs the consent form. As soon as the patient has signed the consent form, they will be given a study code and will be identified by the study code in all the study materials. The relationship between his identity and the study code will be kept in the health care center and will only be available to those who need it to fulfill their duties. Data collected in this pragmatic study is considered codified data. IDIAPJGol has license to use REDCap and the data is collected and held in IDIAPJGol servers, which comply with the European and national requirements. Data controller will be the institution (IDIAPJGol) for the study-related data and the health care institution for the health data collected to manage the patient in clinical practice. There will not be any transfer of data. Only the investigator team will have access to study datasets, and always with codified information to preserve the confidentiality of the participants involved. All the recruiting investigators will have access to REDCap platform to collect the data, each of them with their own specific credentials, and they will only have access to the patients recruited in their own setting. We will follow the FAIR (Findable, Accessible, Interoperable, and Reusable) principles: all datasets and publications will be identifiable by using a “Digital Object Identifier (DOI)” and we will share the data (as far as possible) in the Zenodo platform. We will publish the results in Open Access journals, and wherever possible, the data will be shared without delay following the Creative Commons License with Attribution (CC-BY) or the “No Rights Reserved” (CC0). Data will be saved and shared using standardized formats (txt, csv, and pdf).

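### Table 3 schedules symptom-diary collection at the intervention-only stopping visit, in conflict with the 14-day diary that the text sets for all participants

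*Protocol article*

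**What the plan says.** **Visit schedule (Participant Timeline, Table 3).** The row "Collection of the symptom diary" has two ticks, one at V2 and one at V5 (day 14). The V2 footnote reads "As soon as the patient feels better, only for patients in the intervention group", and the column is headed as starting from day 1. The row "Decision to stop antibiotic course" is ticked at V2 and nowhere else. The row "Hand-out of the symptom diary" is ticked once, at V1 (day 0).

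**Outcome text (Outcomes Collected From the RTI Symptom Diaries).** The rule there makes no distinction between arms: "Participants will rate symptoms for 14 days and return the diary upon completion". The diary outcomes "will be calculated for each participant every day from day 0 until day 14 or when the participant has scored 0 for every item", whichever is earlier. For patients whose diary does not come back, a short form is completed by telephone at day 14. It covers days of antibiotic use, antibiotics taken after the doctor had stopped them, and the duration and severity of symptoms.

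**Timeline text (Participant Timeline, day-by-day list).** Return of the diary is requested at the day 14 call, again for both arms. The description of the intervention visit covers symptoms, vital signs and CRP, and does not mention the diary.

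**Format (Collection of the Participant Data).** "All patients will be able to choose between the web-based and paper version of the symptom diary".

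**The concern.** The table and the text give a site two different instructions, and the difference falls on one arm. Controls have no V2, so their diary stays with them to day 14 under either reading. An intervention patient with a paper diary keeps it to day 14 under the text. Under the table, the diary may be handed over on the day antibiotics are stopped.

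The days after stopping are the ones on which the daily symptom course matters most in this trial. If the diary is gone, four outcomes are exposed: the day 7 total score, the duration of severe symptoms, the duration of moderate symptoms, and the time to total resolution. The last three depend on the last day on which a given score is recorded, so they cannot be determined from a diary that ends while symptoms continue.

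The safety net may also miss these patients. The short form is reserved for diaries that are not returned, and one handed in at V2 could be logged as returned.

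**Working it through.** This is mainly a comparison of passages. The only arithmetic is a count of diary days.

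**1. Is the V2 tick compatible with the text?**

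| Item | Table 3 | Text |
|---|---|---|
| Hand-out | V1 only | Day 0 |
| Collection, control arm | V5 (day 14) | Day 14 |
| Collection, intervention arm | V2 and V5 | Day 14 |
| Re-issue after V2 | None listed | Not mentioned |

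Taken as physical collection, the V2 tick conflicts with a 14-day diary returned on completion. It also leaves nothing to collect at V5. Taken as inspection, it conflicts with nothing, but the row label says collection.

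**2. Could a site plausibly take the diary?** Yes, for three reasons.
- V5 is a telephone call. After day 0, V2 is the only scheduled face-to-face contact, and the retention section expects paper diaries to be submitted to the GP and some not to arrive.
- Feeling better is not the same as having no symptoms. The Limitations section says it may mean partial improvement and that cough may persist. Many diaries would therefore not yet have reached 0 on every item at V2.
- Under Interventions, a patient who does not meet the stopping criteria continues for 2 more days and may be reassessed. A diary kept at a first V2 could thus be gone while treatment is still running.

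**3. Size per affected diary.** The planned length is 14 days. The day of V2 is not given, so day 3 to 5 is assumed. Days lost = 14 − day of V2, counting the day of V2 as recorded.
- Day 3: 14 − 3 = 11; 11/14 = 79%
- Day 4: 14 − 4 = 10; 10/14 = 71%
- Day 5: 14 − 5 = 9; 9/14 = 64%

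For any V2 before day 7, the day 7 score is missing. The abstract has entries made in the evening, so a daytime visit would cost one further entry.

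**4. Number affected.** The count is 237 (intervention arm, Sample Size) × the share using paper × the share attending V2 × the share whose site keeps the diary. None of the three shares is given, so the number can lie anywhere between 0 and 237. If every patient used the web diary, or every site only looked at the paper one, it would be 0.

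**5. What does not depend on the diary?**
- The primary outcome is assessed by a doctor in the day 14 call.
- Antibiotic duration is also checked in electronic medical records.
- Use of other antibiotics is asked about in the day 7 and day 14 calls.
- Reattendances and complications come from case report forms and calls to day 28, cross-checked with clinical records.

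The sample size (402 evaluable, 474 enrolled) rests on the primary outcome and is untouched.

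**The case against.** The strongest reply is that the plan already states the right rule. The text sets 14 days and day 14 return for everyone, the V5 tick carries no arm restriction, and the description of the intervention visit says nothing about taking the diary. Looking at the diary at V2 and retrieving it at day 14 fits every passage. A hand-in on day 3 is also not a completed diary, so a careful site would still complete the short form. Web diaries cannot be taken away at all.

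Much of this stands. It shows that the protocol does not intend intervention diaries to end at stopping. It does not remove the conflict, because the table says collection and visit schedules are what sites work from.

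A reader might infer more: that symptom durations and antibiotic days in the intervention arm will look shorter, that relapse will go unseen, and that the bias favours the intervention and cannot be repaired. The documents do not support this.
- Relapse, resumed or other antibiotics, and treatment duration have the non-diary sources listed above. Only the daily symptom scores depend on the diary alone.
- A diary that stops early produces missing values, not favourable ones. The day 7 score would be absent rather than lower. Durations would look shorter only if unrecorded days were analysed as symptom-free or the last recorded day were used as the end of symptoms, and the article says neither.
- The short form could still recover overall duration and severity of symptoms by recall, provided it is triggered.

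**Conclusion.** The inconsistency is real and should be reconciled. Table 3 schedules diary collection at a visit that only the intervention arm has, with no re-issue, while the text requires a 14-day diary in both arms. The consequence is a conditional risk: if a site follows the table literally with a paper diary, daily symptom scores after V2 are missing in one arm only, and the day 14 short form may not be triggered.

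The illustrative loss is 9 to 11 of 14 days (64% to 79%) per affected diary. It assumes V2 on day 3 to 5, a paper diary, and a site that keeps it. The number of patients affected cannot be estimated from the document. The direction of any bias is not fixed, because it depends on how unrecorded days are handled. The exposure is limited to secondary symptom outcomes, and the noninferiority comparison is not threatened. One-arm loss of symptom data in an open-label trial is still worth preventing when prevention is this cheap.

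**What to change.** 1. In Table 3, remove the diary-collection tick at V2, or give it its own row labelled *diary reviewed and left with the patient*.
2. State in the table and the site instructions that the diary is collected at day 14 in both arms.
3. State that a diary ending at V2 before all items score 0 counts as not returned, so that the day 14 short form is completed.

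The cost is one table edit and one or two lines of site instruction. It needs no extra visits, patients or staff, and no change to the sample size. If recruitment has begun, a clarification to sites does the same job, with a check for diaries already taken at V2.
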